## PROTOCOL

### **Study title: Randomised controlled trial of a multimodal couple-coping intervention to enhance couples' sexual adjustment after treatment for premenopausal breast cancer**

#### **i. Research context**

Breast cancer (BRC) refers to cancer originating from breast tissue. BRC can occur in both genders, 99% of BRC occurs in women [1]. Given that the breast is regarded as a symbol of femininity and sexuality in women, a diagnosis of BRC and its related treatment have significant impacts on body image and sexual health [2,3].

The World Health Organisation (WHO) defines sexual health as physical, emotional, mental and social well-being with respect to sexuality [4]. It has three main dimensions: sexual function, sexual self-concept and sexual relationships [5]. Sexual function embraces the sexual response cycle during intercourse, including sexual desire, excitement, plateau, orgasm and resolution [6]. Sexual self-concept is the image of oneself as a man or a woman, and the evaluation of one's adequacy in masculine or feminine roles. Sexual relationships are the interpersonal situations in which one's sexuality is shared with another [5]. Sexual health is also intimately connected to body image, which involves thoughts, feelings and behaviours related to one's appearance and functioning. Body image disturbance resulting from cancer and its treatment includes important sexual aspects of altered appearance, sensory changes and functional impairment [7].

BRC and its treatments affect sexual health through several mechanisms. Surgery is the first-line treatment for BRC, in which breast tissues are removed. For most women, breasts and nipples are integral to their feminine identity, and they also play important roles in sexual excitement [3]. Patients report disrupted body image, and various sexual problems after surgery including loss of breast sensation, less sexual desire and arousal, and painful sensations over the breast, chest and shoulders which interfere with sexual activity [8,9]. Adjuvant therapies – chemotherapy, radiation therapy and endocrine therapy – also have adverse effects. Chemotherapy alters body image through hair loss and impairs sexual desire and arousal due to cytokine-related fatigue [10,11]. Chemotherapeutic agents also induce oestrogen blockade in premenopausal women leading to vaginal dryness, decreased sexual desire, painful intercourse and difficulty in reaching orgasm [3,8,9,12]. Radiation therapy can cause skin burning and scarring of the breast, which adversely affects body image and sexual activity. Endocrine therapy decreases sexual desire and causes vaginal dryness, which impair sexual function. These changes all adversely affect intimacy and relationship quality [8]. Such problems are found to be more prominent in BRC women below 50 years because of medication-induced menopause and possibly due to more aggressive and toxic treatments [3,13].

Women with BRC under age 50 report more treatment-related side effects and are more vulnerable to long-term sequelae [3,14]. Of the BRC cases in Hong Kong, around 34% are diagnosed under age 50, which is the median age women reach menopause [15,16]. After completion of BRC treatment, only 22% of premenopausal women had a natural menopause while the others encountered medication-induced menopause with multiple sexual problems including lack of sexual desire, vaginal dryness, and difficulty with arousal, enjoyment or orgasm. These problems often persist beyond five years post-treatment [14]. Living with BRC and its aftermath therefore requires considerable sexual adjustment to re-establish and maintain a satisfying sexual relationship.

Partners of cancer patients also report many challenges after diagnosis and treatment. A study recruited 122 partners, including both male and female to explore the impact of cancer and its treatment on their sexuality and sexual relationships [17]. Most partners (78%) of women with BRC reported alterations in sexuality, with complete cessation of sex or a marked reduction in the frequency of sex after treatment. Perceptions of loss of intimacy made them feel sad. However, only 20% of the

participants were afforded the opportunity to discuss sexuality with a healthcare professional [17]. Intimacy is a key component of relationship quality and could buffer psychological distress [18]. Partners experience psychological distress but their sexual health needs are neglected [17,19]. During treatment, partners are critical to helping women adjust to their illness and offer invaluable support [17,18]. Partners assume the role of carers and people with cancer are repositioned as patients, which subsequently influences sexual relationships due to exhaustion from the caring role, and can lead to relationship discord [12,17]. In addition, as resumption of usual sexual function after treatment for BRC can be difficult, or is sometimes impossible, renegotiation of sexual health with involvement of a supportive partner, is needed to facilitate adjustment to illness [12,17,19], help rebuild intimate relationships and thus improve quality of life (QoL) [20].

Couple-based interventions have yielded significant benefits for sexual health outcomes in other fields and warrant investigation in the BRC context [8,18,21]. Couple-based interventions refer to intervention delivered to couples currently married or living together [21]. Evidence from research on the effects of couple-based interventions for sexual problems following BRC has demonstrated positive results on improving sexual function in terms of orgasm and intimacy, sexual and relationship satisfaction, body image, couple communication, dyadic coping, adjustment and QoL of both patients and their partners [8,18,21]. Providing and receiving support from each other during couple-based interventions promotes joint problem-solving and shared coping [18]. Positive partner coping enhances sexual adjustment and achieves a positive couple relationship [21]. Conventionally, couple-based interventions are delivered in face-to-face mode. However, this format is restricted in pandemic situations. With the popularity and increased recognition of electronic usage of healthcare services, online-based or mobile interventions are viable alternatives to face-to-face delivery of sexual health care [13,22]. It is suggested to be more effective if the delivery mode is adjusted to the needs of patients. In view of the importance of establishing a rapport between clinician and patient, a combination of face-to-face and online modes would be appropriate to address sexual health concern in a comfortable atmosphere [13]. No study has investigated the effects of a multimodal couple-based intervention, with combination of face-to-face and online modes, on sexual health outcomes, and no similar study can be found in PubMed, Cochrane Library or trial registries (ClinicalTrials.gov and ISRCTN).

Given that the previous type and quality of sexual activity is often altered after treatment for BRC [12,17,19], flexibility in sexual renegotiation is regarded as a central aspect of couple-based interventions to address sexual health concern in the context of cancer [19]. The Model of Flexible Coping with Sexual Concerns provides the philosophical underpinning of the proposed intervention. It enables responsive intervention delivery, adapted to need, by expanding the conceptualisation of sexual function and activity, adopting positive coping strategies, and shifting the focus on sexual functioning to intimacy, subsequently bringing beneficial effects on sexual adjustment and relationship satisfaction [23]. It is posited that discussion of flexibility in coping with sexual health concern early in the treatment trajectory facilitates sexual adjustment and the renegotiation of intimate relationships during survivorship. The intervention components integrate evidence-based techniques from cognitive behavioural couple therapy and sex therapy for intimacy enhancement [24], combined with psychoeducation, skills training and therapeutic counselling [21], in order to motivate the change of sexual function and activity in cognitive and behavioural aspects [23]. With flexible coping with sexual concern, individuals can think about sexual activity differently and engage in attainable sexual activities to maintain and foster intimacy [23]. The causal model is illustrated in Appendix A.

In summary, women treated for BRC, particularly those diagnosed and treated premenopausally, and their partners, report many persistent sexual problems and experience relationship challenges post-treatment. Sexual health issues are complex and interrelated and reciprocally influence intimacy and relationship quality [8]. Sexual health and intimacy have significant implications for QoL that determines overall wellbeing [13,19]. Therefore, WHO emphasises that sexual health warrants attention in cancer

care so that QoL can be improved [8]. However, sexual health is a neglected area in clinical practice, for both patients and partners. It is timely to develop an empirically-based and theory-driven flexible couple-coping intervention to address sexual health concern among premenopausal BRC patients and their partners in Hong Kong.

The study is led by an established team of researchers and nurse clinicians who specialise in cancer care and are committed to the wellbeing of women after cancer treatment. The principal investigator (PI) and co-investigators (Co-Is) have worked and published together in cancer research for many years to explore sexual health issues and to develop interventions to improve psychosexual wellbeing in women treated for gynaecological cancer [25-30], with notable success in recruitment, implementation and translatable outcomes. Previous collaborations amongst PI and Co-Is underpin all aspects necessary for this study. Collectively, the team has access to oncology clinic of many public hospitals in Hong Kong. As to methodology, the PI has obtained collaborative support from the Co-Is and a statistician with expertise in quantitative and qualitative data analysis as a Co-I in this study. As to professional qualifications, the PI has postgraduate qualifications in sexuality counselling and psychotherapy.

## **ii. Research questions**

The number of premenopausal women with BRC is growing. These women and their partners experience persistent treatment-related sexual health concerns and unmet sexual health needs. This study aims to develop and implement a novel multimodal couple-coping intervention (MCI) for this cohort in Hong Kong. The research questions are, compared to controls:

1. What are the effects of the MCI on the primary outcome of sexual adjustment in premenopausal BRC women after completion of the intervention, three-month and six-month post-intervention?
2. What are the effects of the MCI on the secondary outcomes of relationship quality and QoL in premenopausal BRC women and their partners after completion of the intervention, three-month and six-month post-intervention?
3. What are participants' experiences of, and compliance with the intervention?

## **iii. Research methods**

A phased-approach will develop, implement and evaluate the MCI. As the newly developed MCI consists of multiple components which interact with each other to achieve the desirable outcomes, it is regarded as a bundled (i.e., complex or multicomponent) intervention [31]. In order to develop an evidence-based complex intervention with an appropriate theory and evaluated rigorously, the Medical Research Council framework is used to guide the process.

### ***Developing a complex intervention***

In this phase, the existing evidence on similar interventions, theoretical framework underpinning the interventions, and the changes of outcome to be expected should be identified [31]. This phase has been conducted and the development of the MCI is based on scientific evidence, theoretical framework and the success of our previous GRF-supported project in women with gynaecological cancer.

According to the Model of Flexible Coping with Sexual Concern [23], a more flexible perception of sexuality for individuals who may not be able to resume or engage in their previous level and type of sexual activity is beneficial. In the context of BRC, enhancing the level of flexibility among women treated for BRC and their partners has potential to promote their sexual adjustment, improve relationship quality and QoL. To increase flexibility, the intervention will adopt three strategies: expanding conceptualisation of sexual function and activity, adopting positive coping strategies, and focusing on intimacy [23]. The components of the MCI include psychoeducation, skills training and therapeutic counselling with the integration of techniques from cognitive behavioural couple therapy and sex therapy [21,24]. The contents and design of the intervention are also guided by the findings of previous studies

[18,21,23,24], and the completed GRF project led by the PI in which factors that might enhance the provision of sexuality care and the information needs of sexual health and preferences for sexuality care of female gynaecological cancer patients were identified [25]. The information needs include possibility and suitable timing of sex life resumption, its potential impact on physical health, adaptation to changes in sex life, and potential impact of disease and treatment on physical, psychological and sexual functioning. Regarding the format, the participants indicated the preference for face-to-face counselling with partner participation during post-operation and rehabilitation, and information delivered via internet with reading materials [25].

The proposed MCI will be an eight-week five-session programme, each session delivered every two weeks (at Weeks 0, 2, 4, 6, and 8), and covering topics on the impact of BRC on sex and intimacy, communication and problem-solving skills, dyadic positive coping, cognitive restructuring of sex and intimacy, intimacy-building activities, and maintaining intimacy [18,21,23-25]. The first and last sessions will be conducted in face-to-face dyad format, the second session will be virtual dyad counselling, the third one will be online reading with chat-based discussion forum and homework exercise, and the fourth will be reminder telephone call for reviewing what has been achieved and scheduling the last session. The counselling sessions will last for 60-90 minutes and delivered by a full-time research nurse who will receive one-week training from the PI to provide the intervention, while the online discussion will be moderated by the research nurse to monitor the progress of sensate focus practice which is a common technique used in sex therapy to improve intimacy and communication between partners around sex. The telephone call will last for around 30 minutes. Components and contents of the MCI are listed in Appendices A and B.

### ***Phase I: Refinement of intervention***

**Design:** In this phase a qualitative approach will systematically explore the acceptability and relevance of the MCI from the perspective of Hong Kong premenopausal women treated for BRC and their partners, a panel of experts including academics specialising in oncology research, and healthcare professionals working in oncology units.

**Sample size:** As recommended by Creswell [32], an expert in mixed-method and qualitative research, 20 to 30 participants form an adequate sample to explore the breadth of a topic in its entirety. We will therefore recruit 10 purposely sampled participants with BRC and their partners (n=20), and 10 experts to form an expert panel for this phase of the study.

**Setting and subjects:** We will recruit four purposive samples: women treated for BRC, their partners, academics specialising in oncology research, and healthcare professionals working in oncology units. A cash allowance of HK\$200 will be given to each dyad to cover travel expenses on completion of this phase of the study.

- i. **Women treated for BRC:** Participants will be recruited from the oncology clinic during their regular follow-ups. The inclusion criteria for recruitment are: women with a diagnosis of BRC; all active treatment completed but endocrine and/ or maintenance therapy allowed; with a regular sexual partner, either heterosexual or homosexual; over 18 years; in a premenopausal state when diagnosed with BRC; has a smartphone with internet connection; able to understand spoken Cantonese and to read Chinese; consenting to participate. Those with a known pre-existing psychiatric illness will be excluded.
- ii. **Partners of BRC women:** Partners of the participating patients will be recruited.
- iii. **Academics:** Academics who specialise in oncology research will be recruited from the institute of the PI. There are six academics working on this research theme and all of them will be invited to join the interviews.
- iv. **Healthcare professionals:** Registered nurses and physicians working in the oncology unit of two participating hospitals, with at least two-year clinical experience in the specialty, will be invited to

join the interviews. Their views and opinions on the MCI would contribute to the accessibility and sustainability of implementation of the intervention in important ways.

**Procedure:** Eligible women will be approached and invited to participate in the study. The first session of the MCI will be delivered after recruitment if the partner is present, or on another schedule. The other four sessions will then be conducted every two weeks. On the completion of the last face-to-face counselling session, a semi-structured interview will be conducted to explore the acceptability and comments on the MCI. An interview guide will be adopted with examples of questions: ‘What’s your general impression of the programme?’ ‘How did the intervention help you cope with changes in sex and intimacy after treatment for BRC?’ and ‘Describe for me how you set goals for sexual adjustment as a result of this programme.’ Participants will be encouraged to provide comments on the intervention. Based on previous experience with this cohort, each interview should last around one hour.

For the participating academics and healthcare professionals, the intervention components, content and design will be illustrated to them during individual interviews at the hospitals or in other venues convenient to the participants. They will be invited to provide comments and suggestions on the intervention, as well as its implementation and sustainability.

**Data analysis:** All interviews will be audio-taped and transcribed verbatim by the research nurse conducting the interviews and verified by the PI against the taped record. The PI, and a Co-I who has rich experience in conducting qualitative research, will carry out data analysis independently by means of content analysis. The PI will discuss any discrepancy in coding with the Co-I and other investigators to achieve resolution. The findings will be used to refine the intervention for next phase of the study.

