**Procedure:** Eligible women and their partners will be approached in the oncology clinic and have the aims of the study explained to them. Information sheets about the study and consent forms will be

provided. After written consent is obtained, the participating dyad's demographic data will be collected and the instruments administered during baseline face-to-face interviews. The participants will then be randomly assigned to either the intervention or attention control group. Subject allocation will be done using stratified block randomisation with a block size of 10. A random sequence of grouping identifiers (I or C), based on computer-generated random numbers, will be prepared in advance by an independent statistician. The grouping sequence lists will be password-protected and stored in a computer, and only be accessible to staff independent of the study or responsible for group allocation. The group allocation of each participant will be assigned according to the sequence of enrolment and the corresponding group identifier in the previously prepared random sequence list. The trained research nurse will deliver the MCI to the participants and their partners. In order to ensure the fidelity of the intervention, the PI will monitor the intervention delivered to the first 10 dyads. Reflective notes and a record of the participants' attendance will be kept as a means of process evaluation. To ensure blinding of the outcome assessor, a part-time research assistant who will not be informed of the group status of the participants will be responsible for reassessment. Reassessment will be conducted at the same time point for both groups, i.e. on the completion of the intervention, three months and six months post-intervention via telephone call. Participating dyads in the intervention group will be invited to be interviewed about their experiences and feelings towards the intervention, and will be audio-taped. Another research nurse will conduct qualitative interviews with the participating dyads to prevent an experimenter effect.

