**Data collection:** Participation and completion rates of the intervention by the participating dyads in the intervention group will be monitored. A demographic and clinical data sheet will be used to record the socio-demographic and clinical characteristics of the participants. Effects of the intervention on the outcome variables will be measured at baseline (T0), on completion of the intervention (T1), three months (T2) and six months (T3) post-intervention by using the following measures:

1. *Chinese version of the sexual adjustment scale of the Sexual Adjustment and Body Image Scale (SABIS)*

The Chinese version of the sexual adjustment scale of SABIS will assess the effect of the MCI on sexual adjustment among the women treated for BRC. The SABIS consists of two scales: a six-item body image scale and an eight-item sexual adjustment scale. Using a five-point Likert scale with scores ranging from 1 to 5, higher scores indicate better outcomes. The scale has been used previously in BRC with good reliability and validity [9]. While no Chinese version is available, we have developed one using the Brislin model of translation and guidelines for cross-cultural adaptation of scales. The translated version of SABIS will be assessed for semantic equivalence and content validity by a panel of six healthcare professionals, with a content validity index of 0.8 or above set as the satisfactory criteria, and revised if necessary, before administration to participants.

2. *Chinese version of ENRICH Marital Satisfaction Scale (EMS)*

The Chinese version of EMS will be used to assess the quality of partner relationships of the participating dyads individually. It consists of 10 items, extracted from the original full-length 125-item ENRICH Marital Inventory, which are recognised as the most important dimensions of relationships by the original author. A five-point Likert scale with scores ranging from 1 to 5 is used, with higher scores indicating better relationships. The scale has established discriminant validity and demonstrated good reliability, with an internal consistency of 0.76 [35].

3. *Chinese version of the MOS 36-item Short Form (SF-36) Health Survey*

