#### 4. Demographic and clinical data sheet

A data collection sheet will record the socio-demographic and clinical characteristics of the BRC women: age, education level, monthly household income, marital status, duration of marriage/current relationships, number of children, religious beliefs, stage of cancer, time since diagnosis, treatment modality and length of treatment. Socio-demographic data of the partners will also be collected: age, education level, medical and drug history.

Qualitative data will be collected from the intervention group through semi-structured interviews up to the point of data saturation, estimated to be 20 participating dyads. Their experiences and perceptions of the MCI, and whether the programme improved their sexual adjustment will be explored. The interviews will be scheduled after the completion of the programme, and audiotaped with consent.

**Data analysis:** Data will be summarised and presented using appropriate descriptive statistics. The homogeneity of participants' characteristics between the two study arms will be assessed using independent t, Mann-Whitney, chi-square or Fisher's exact tests, as appropriate. Intention-to-treat principle will be adopted in the outcome analysis by using a generalised estimating equations (GEE) model to compare the differential changes in each outcome across the four time points between the two arms. All statistical analyses will be performed using SAS release 9.4 (SAS Institute, Cary, NC.). All statistical tests are two-sided with level of significance set at 0.05. Audiotapes of the interviews will be examined by means of content analysis. First, the recorded tapes will be transcribed verbatim. All transcripts will be compared with the recording to check for any discrepancies, and revised as necessary. The transcripts will then be content analysed to identify persistent words and code themes within the data. Finally, significant categories and themes of the data will be formulated and confirmed by the PI and Co-I to improve its accuracy, and then translated into English [37].

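### Phase I couples are interviewed on acceptability only after the last session, with no route to the views of couples who stop earlier; the Phase II interview wording may lean the same way

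*Protocol*

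**What the plan says.** Phase I tests the acceptability and relevance of the MCI before the trial. Its sample is given under Phase I, Sample size: "We will therefore recruit 10 purposely sampled participants with BRC and their partners (n=20), and 10 experts to form an expert panel". The Procedure sets one interview for couples: "On the completion of the last face-to-face counselling session, a semi-structured interview will be conducted to explore the acceptability". The last face-to-face session is the fifth, at Week 8 (section on developing the intervention). The experts are interviewed separately, after the components have been shown to them: "They will be invited to provide comments and suggestions on the intervention, as well as its implementation and sustainability". The Phase I Data analysis paragraph then states the use: "The findings will be used to refine the intervention for next phase of the study".

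Research question 3 reads: "What are participants' experiences of, and compliance with the intervention". Three places in Phase II bear on it.
- Procedure: "Participating dyads in the intervention group will be invited to be interviewed about their experiences and feelings towards the intervention". It also provides for an attendance record and reflective notes.
- Data collection: "Participation and completion rates of the intervention by the participating dyads in the intervention group will be monitored".
- The text under the demographic and clinical data sheet, which estimates about 20 dyads to saturation: "The interviews will be scheduled after the completion of the programme, and audiotaped with consent".

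The Ethical issues section gives participants the right to withdraw at any time. Neither phase describes an interview at discontinuation or a record of why a couple stopped.

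**The concern.** An acceptability study learns most about unacceptability from those who did not continue. If the interview is triggered by finishing, the couples best placed to say that a component was unwelcome, badly timed or too demanding are the ones without a trigger. The MCI includes joint counselling and sensate-focus practice, intimate components on which dissenting views matter.

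Two uses of the interviews are at stake. The Phase I findings shape the version of the MCI that goes into a 160-dyad trial, so a component that puts couples off could pass through without comment from recipients. In Phase II, the answer on participants' experiences could look more favourable than the experience of the whole intervention group.

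**Working it through.** **The plan's own figure.** The trial size does not depend on this point, but it reproduces. A two-sample t-test with effect 0.5 SD, two-sided 5% and 80% power needs 63.77 per group, so 64 (power 80.1% at 64). Allowing for 20% attrition gives 64 / (1 − 0.20) = 80 per group, 160 in all.

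**Phase I, step by step.**
1. The trigger is the end of session five. A couple that stops at session two or three does not reach it.
2. No alternative trigger is written.
3. The second source for refinement is the 10 experts. They comment on components, content and design, but have not received the MCI and cannot report what recipients felt or why a couple stopped.
4. Recipient feedback for refinement therefore comes from completers if the text is followed.

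**Phase II, step by step.**
1. The Procedure invites intervention-group dyads and states no attendance condition.
2. The later text says when interviews are scheduled, not who is eligible.
3. Completion can mean a dyad's own completion or a calendar point. The Procedure supports the calendar reading: both groups are reassessed at the same time point, on completion of the intervention, and controls have no MCI sessions to complete.
4. The wording thus permits interviews with dyads that stopped, but does not require any among the roughly 20.

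**What the other sources supply.** Attendance and completion rates show that a dyad stopped, not why. The protocol does not say who writes the reflective notes or that they hold the couple's own account. The reassessment questionnaires measure sexual adjustment, relationship quality and quality of life, not experience of the MCI.

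**Scale (assumption).** The protocol gives no session-stopping rate; its 20% is attrition from the trial. Let p be the share of couples who stop early, taken as 5% to 30%, with couples independent.

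| p | Phase I stoppers, 10 × p | Chance of at least one, 1 − (1 − p)^10 | Stoppers among 80 MCI dyads, 80 × p | Expected in 20 dyads taken regardless of attendance, 20 × p |
|---|---|---|---|---|
| 5% | 0.5 | 40% | 4 | 1 |
| 10% | 1 | 65% | 8 | 2 |
| 20% | 2 | 89% | 16 | 4 |
| 30% | 3 | 97% | 24 | 6 |

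The Phase I columns give the couples without an interview trigger. The Phase II columns show only how many stoppers might exist; they do not count dyads excluded by the protocol.

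**The case against.** The strongest reply is that the protocol excludes nobody in Phase II. The invitation is unconditional, and the calendar reading of completion fits the rest of the text. This stands: a reader might infer that couples who stop are never asked in either phase, or that up to 16 of 80 dyads are excluded, but for Phase II the documents do not say so.

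Three other strong readings also fail.
- Research question 3 is not answered from compliers alone. Its compliance half uses participation, completion and attendance data, which cover dyads that stop.
- Refinement does not rest only on couples who finished, because 10 experts also comment, though not as recipients.
- Nothing in the protocol says that sessions upset couples or cause stopping. Distress is one possible reason among several.

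It can also be said that relationship or mental-health deterioration in dyads that stop could show in the Phase II reassessments, which are analysed by intention to treat. That is fair for outcomes, but it gives no account of the intervention itself and does not help Phase I. Finally, the interviews are for content analysis, not for estimating a proportion, so a numerical bias in the share of couples finding the MCI distressing has no basis here. What survives is the Phase I gap and the unclear Phase II wording.

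**Conclusion.** The point holds in a limited form. For Phase I it follows from the text: acceptability feedback from recipients is collected only at the end of the last session, so it comes from completers and may overstate acceptability. For Phase II it is a risk created by unclear wording and the absence of a sampling rule by attendance, confined to the experience half of research question 3.

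The size is unknown. Under the assumed 5% to 30%, 0.5 to 3 of 10 Phase I couples would be missed, which matters in so small a sample. The direction of the bias assumes that couples who stop regard the MCI less favourably than those who finish; this is plausible but not documented. The GEE comparison of the primary outcome and the sample size are untouched. This is a low-cost improvement, not a threat to the trial's main result.

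**What to change.** 1. **Phase I, Procedure.** Hold the couples' interview at completion or at discontinuation, whichever comes first. Offer it as voluntary, with neutral questions suited to couples who stopped. Two of the three example questions presuppose benefit or goals set through the programme; only the one on general impression carries over unchanged.
2. **Phase II, interview text under the demographic and clinical data sheet.** State that completion of the programme means the end of the eight-week period whatever the attendance, and purposively include some non-completing dyads among the roughly 20 planned. No fixed quota is proposed, since the protocol gives no stopping rate to base it on.
3. **Attendance record.** Add a voluntary reason for stopping in the couple's own words. The record is described only for Phase II; the same entry should be kept in Phase I.

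Cost: small changes to the consent and interview-guide wording. The planned interview numbers (10 couples, then about 20 dyads) can stay. Some couples who stop will decline, and slightly fewer completers will be interviewed in Phase II.
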